### 2.7 Statistical analysis

The obtained data will be analyzed using descriptive statistics, such as on prevalence of post-COVID-19 condition including 95% confidence intervals. To assess prevalence, participants tested negative are also presented, providing some insight of “background risk,” as symptoms of post-COVID-19 condition may be nonspecific and present in the general population (41, 42). Prevalence of reported symptoms in post-COVID-19 condition participants will be compared to the prevalence in PCR negatives. Post-COVID-19 incidence will be estimated when follow-up data is available, by determining the proportion of newly diagnosed participants (since baseline) meeting the post-COVID-19 condition criteria. Multivariable models are used to test for the likelihood of (long-term) symptoms in positive vs. negative participants, adjusted for possible confounders. Possible confounders include age, sex, underling disease, severity of COVID-19, and year-quarter when tested. Risk factor analyses, with post-COVID-19 condition as outcome, will be performed using multivariable logistic regression models. Various sensitivity analyses will be performed, e.g., by only including participants with highest certainty score 0. These are examples of analyses to answer a main study question. Appropriate statistical analyses will be performed to answer all study questions.

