## 2. Methods and analysis

The aim of our study is to understand the prevalence, incidence, risk factors and impact of post-COVID-19 condition.

The following study questions will be addressed:

What is the prevalence and incidence of post-COVID-19 condition in PCR confirmed SARS-CoV-2 positive adults, by various definitions, accounting for occurrence of symptoms in negative tested adults?What are sociodemographic and medical risk factors (for example vaccination status and virus variant) for having, preserving, and recovering from post-COVID-19 condition?What is the impact of having post-COVID-19 condition on negative health outcomes and socioeconomic aspects, including social, labor, and educational participation?What is the role of having post-COVID-19 condition in maintaining positive health, including social, mental, emotional, and physical health?How can health be promoted in relation to post-COVID-19 condition, using tools from medical and other types of care, in recovery and coping with post-COVID-19 condition?

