### 2.3 Recruitment

Emails to invitees were send between 17 and 25 November 2021. Invited for participation were 41,780 PCR COVID-19 positives and 19,875 negatives from test records registered in the registry. Invitees received an email containing the invitation for participation, study information with a link to the website (containing the participant information and email address in case of questions), and a weblink to the online questionnaire.

Participants needed to be able to understand, read and write the Dutch language, as all materials were provided in Dutch.

Digital informed consent was asked before the questionnaire started. Further digital informed consent was asked to link data from the questionnaire to the registry data (age, sex, municipality, date of test, and test result).

A reminder was sent 1 and 3 weeks after the invitation to invitees who did not respond to the invitation or started but not completed the questionnaire. The questionnaire was made available using the MWM2 application of market research platform Crowdtech (ISO 27001 certified).

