### 2.6 Data analysis

#### 2.6.1 Primary outcomes in analysis

The time frame for collecting the primary outcomes (summarized below) runs from the baseline questionnaire up to at least 2 years thereafter, assessed at regular intervals.

The main primary outcome:

Post-COVID-19 condition: the symptoms that are defined by the WHO-definition of post-COVID-19 condition, as well as other types of definition. These include a range of symptoms measured at various time points, for example, the presence of at least one symptom 3 months after testing or when filling in the questionnaire, and experiencing of dyspnea (modified Medical Research Council; mMRC) or fatigue (Checklist Individual Strength—subscale subjective fatigue; CIS).

Other primary outcomes include:

Mental health: negative health outcomes related to mental health such as depression (assessed by PHQ-9 scale) and trauma.Social health: negative health outcomes related to social health, such as loneliness (assessed by De Jong-Gierveld scale).Physical health: negative health outcomes related to physical health such as non-communicable chronic diseases (assessed upon self-report on a checklist of conditions present), health index/quality of life (assessed by EQ-5D-5L) and physical activity (assessed by IPAQ).Positive health: experienced general health (assessed by 5-point scale ECHI).

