### 3.1 Strengths and limitations

A major strength of this cohort study is the design comprising of a retrospective and prospective element. In general, including a large population-based sample is a strength, as large sample sizes promote precision and reliability of prevalence estimates and associations between post-COVID-19 condition and risk factors (43). By including a population-based sample we were able to minimize selection bias toward the inclusion of specific groups, such as hospital-based populations. Moreover, including PCR test-negative individuals to determine long-term symptoms and impact of the COVID-19 pandemic in general, made it possible to identify symptoms and impact accountable to a SARS-CoV-2 infection. Matching test-negatives to test-positives on key characteristics (i.e., sex, age, and year-quarter of testing) when sampling limits possible confounding by accounting for the distribution of these characteristics. Finally, a wide range of physical, emotional, social, and behavioral aspects will be mapped using extensive questionnaires, including multiple standardized and validated questions on diverse topics. Doing so enables us to approach post-COVID-19 condition holistically, and to correct future analysis for several confounding factors. By the comprehensive assessment in the current study, post-COVID-19 condition will be classified by several definitions put forward in the literature. These definitions will be compared with each other, and with the established case definition provided by the WHO as well.

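### Section 2.7 compares symptom prevalence in participants classified by their symptoms with that in unselected PCR negatives, so part of the excess is built in and cannot serve as the background correction

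*Protocol article*

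**What the plan says.** Study question 1 (section 2) asks for the prevalence and incidence of post-COVID-19 condition in PCR-positive adults, "accounting for occurrence of symptoms in negative tested adults". Section 2.6.1 makes the condition the main primary outcome and builds it on symptoms: "the symptoms that are defined by the WHO-definition of post-COVID-19 condition, as well as other types of definition". One example given there is "the presence of at least one symptom 3 months after testing or when filling in the questionnaire"; dyspnoea (mMRC) and fatigue (CIS) are named as well.

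Section 2.7 presents the negatives as a view of background risk, because "symptoms of post-COVID-19 condition may be nonspecific and present in the general population". The next sentence is the one at issue: "Prevalence of reported symptoms in post-COVID-19 condition participants will be compared to the prevalence in PCR negatives". Further on, the same section plans a different contrast: "Multivariable models are used to test for the likelihood of (long-term) symptoms in positive vs. negative participants, adjusted for possible confounders". Section 3.1 says that including test-negatives "made it possible to identify symptoms and impact accountable to a SARS-CoV-2 infection".

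**The concern.** A participant enters the first group of the section 2.7 comparison by reporting symptoms. A PCR negative enters the second group whether or not any symptom is present. The grouping rule and the outcome are the same kind of information, but the rule is applied to one side only. The resulting difference mixes any effect of infection with the effect of the selection, and the two cannot be separated afterwards.

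The sentence directly follows the one on background risk, so a reader will naturally take it as the step that allows for background symptoms. It does not do that. Background symptoms in positives are counted in full among the cases, while the negatives' figure is diluted by everyone without symptoms. If the comparison is reported as written, a table of symptoms in cases against negatives could be read as showing what infection causes, when an excess would be there with no effect at all.

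**Working it through.** **Plan's own figure.** The article states no expected prevalence, effect size or power for this comparison, so there is nothing to reproduce. The invitee counts in section 2.3 ("Invited for participation were 41,780 PCR COVID-19 positives and 19,875 negatives from test records registered in the registry") agree with Table 1: 41,780 + 19,875 = 61,655, of which 41,780 / 61,655 = 67.8% are positive.

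**Inputs**
- Index group: participants meeting a symptom-based definition D (sections 2.6.1 and 2.7).
- Reference group: all PCR negatives, with no symptom criterion (section 2.7).
- b: share of negatives with at least one symptom. The article gives no value, so 10% to 90% is assumed.
- p_s: share of negatives with a given symptom s on the list.

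**No-effect case, definition of any one symptom.** Suppose positives and negatives have the same symptom distribution, and that the list and time point used to define the condition are also used for the comparison.

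- Any symptom: 100% of cases against b of negatives. The false excess is 1 − b.
- Symptom s: every person with s meets D, so its prevalence among cases is p_s / b. The false ratio is (p_s / b) / p_s = 1 / b.

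For example, with b = 20% and p_s = 4%, prevalence is 4 / 20 = 20% among cases against 4% among negatives. The ratio is 5.0 and the difference 16 points, with no effect of infection.

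| b (assumed) | False ratio per listed symptom, 1/b | False excess for any symptom, 1 − b |
|---|---|---|
| 10% | 10.0 | 90 points |
| 20% | 5.0 | 80 points |
| 30% | 3.3 | 70 points |
| 40% | 2.5 | 60 points |
| 50% | 2.0 | 50 points |
| 70% | 1.4 | 30 points |
| 90% | 1.1 | 10 points |

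**Other definitions.** In general the no-effect ratio is P(s | D) / P(s). If D is fatigue alone, the ratio for fatigue is 1 / P(fatigue). For another symptom it is above 1 if that symptom goes with fatigue, and 1.0 if the two are independent. The size then depends on the correlation with the defining symptoms, not on b.

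**Check by simulation, no effect of infection.** There were 10 or 20 correlated symptoms (latent correlation 0.4) at 5% or 10% each, an assumed 10% or 20% of invitees responding, and 200 replicates.

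| Background share with any symptom | Cases v all negatives, ratio | 1/b |
|---|---|---|
| 28% | 3.6 to 3.7 | 3.6 |
| 39% | 2.6 | 2.6 |
| 58% | 1.7 | 1.7 |

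In the same data, all positives against all negatives gave ratios of 1.00 to 1.03.

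**Same criterion on both sides.** If cases are compared only with negatives who also meet D, both sides equal p_s / b under no effect and the ratio is 1.0.

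**The case against.** The strongest reply is that section 2.7 already contains the right contrast. The adjusted models compare positive with negative participants, with neither side selected on symptoms. A reader might infer from the faulty sentence that the whole use of the negatives is circular. The article does not support that: the models stand apart from this comparison, and the section calls its analyses examples. The claim in section 3.1 about attributing symptoms to infection rests on including negatives in general, not on this sentence. This part of the reply stands and limits the point to the one comparison. It does not repair the sentence, because both results would be reported and they differ even when infection does nothing.

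Second, a reader might infer that every symptom must look more common after COVID-19 whatever the truth, or that false-positive tests are planned. Neither follows. The section attaches no test to this sentence. Any one symptom is only one example definition. A symptom unrelated to a fatigue-based definition need show no excess. Someone who qualified by symptoms 3 months after testing may report none at the questionnaire. The 1/b result is therefore specific to its stated conditions, and it is small when background symptoms are very common.

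Third, the wording may be shorthand for all PCR positives. That is possible, but the same section writes of positive and negative participants when it means the test groups. If shorthand was intended, the sentence still needs the same correction.

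**Conclusion.** The concern holds for the descriptive comparison in section 2.7, and only for that. As written, it selects one group on symptoms and leaves the other unselected. It therefore cannot stand as the background correction asked for in study question 1.

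The false ratio of 1/b rests on three assumptions: the any-one-symptom definition, the same symptom list and time point for definition and comparison, and no effect of infection. Because b is unknown here, the honest statement is a range: substantial if up to about half of negatives have some symptom (2.0 or more), modest at 70% (1.4) and slight at 90% (1.1). For the WHO, fatigue and dyspnoea definitions no single figure can be given. The adjusted positive against negative models do not share this fault. This is a stated analysis that would mislead if followed, not a detail left to a fuller plan.

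**What to change.** Replace the sentence in section 2.7. Compare symptom prevalence between all PCR positives and all PCR negatives, using the same symptom definition and comparable time since test, and report the difference and ratio with 95% confidence intervals, overall and per symptom. Time since test needs attention because the invited groups differ: Table 1 puts 1.8 + 11.4 = 13.2% of negatives but 0.1 + 1.7 = 1.8% of positives in the second and third quarters of 2020.

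Present the symptom profile of participants meeting the condition definition as description without a comparator. Alternatively, compare it only with negatives meeting the same symptom criterion, and say that this describes symptom pattern rather than excess.

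No new data are needed. Table 2 shows that symptoms when tested, symptoms now, severity and duration were asked of all participants. Course of symptoms was asked of positives only, so it cannot form part of the shared definition. The cost is one sentence, slightly more analysis work and a less striking contrast.

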### 2.5 Data collection

Data are collected by online self-administered questionnaires. The baseline questionnaire could be filled in between 17 November 2021 until 9 January 2022. The questionnaire contained a range of factors, including health-factors and health-conditions (Table 2). At baseline, information on the current situation as well as historical information (such as symptoms between the test and the current date) was collected from the participants. Several in-depth questions were only deemed relevant for positives or negatives, and thus not asked to all participants to minimize unnecessary load.

**Table 2 T2:** Topics and questions implemented in the questionnaire of the baseline recruitment of the prevalence, risk factors and impact evaluation of post-COVID-19 condition (PRIME post-COVID) study.

**Topic**	**Questions**	**Asked to**
Demographics	Sex	All
	Year of birth	All
	Postal code	All
	Residential situation	All
	Relationship status	All
	Level of education	All
	Country of birth	All
COVID-19 test data	Test result	All
	Test date	All
	Vaccination status	All
	Vaccination date(s)	All
	Vaccination type(s)	All
	Presence of antibodies	Negatives
Experienced symptoms	Symptoms when tested	All
	Symptoms now	All
	Severity of symptoms	All
	Duration of symptoms	All
	Course of symptoms	Positives
	Subjective assessment of degree of recovery	Positives
	Subjective assessment of having post-COVID-19 condition	Positives
Use of professional medical care	Treatment when tested (hospitalization, duration, and oxygen use)	Positives
	Received care since test	All
	Reason for received care	Positives
Lifestyle	Smoking and substance	All
	Physical activity [international physical activity questionnaire; IPAQ (26)]	All
Experienced physical and mental health	Underlying disease	All
	Origination of underlying disease	All
	Overall general health	All
	Quality of life [EQ-5D-5L (27)]	All
	Dyspnoea [modified Medical Research Council; mMRC (28)]	All
	Fatigue [checklist individual strength—subscale subjective fatigue; CIS (29)]	All
	Mental fatigue [self-constructed based on CIS-Fatigue (30)]	All
	Coping [cognitive emotion regulation questionnaire; CERQ (31)]	All
	Trauma [PTSD checklist for the DSM-5; PCL-5 (32)]	Positives
	Depression [patient health questionnaire-9; PHQ-9 (33)]	All
	Loneliness [De Jong-Gierveld (34)]	All
Labor participation	Labor participation [work productivity and activity impairment; WPAI (35)]	All
Social participation	Membership to clubs	All

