**Figure 2 F2:**
[figure not shown]
Decision tree to ascertain certainty assessment scores based on self-reported and public health registry data.

Furthermore, it cannot be formally ruled out that the negative PCR-tested participants, who also did not report COVID-19 antibodies pre-vaccination, might include some COVID-19 positive cases. The absence of SARS-CoV-2 antibodies does not guarantee that an infection did not take place since some people (often mild cases) do not show sero-conversion and also sero-reconversion occurs over time (37–40). We will take reported antibody status in PCR negatives into account when estimating the prevalence of experienced symptoms.

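### Severity of COVID-19 is named as a possible confounder for the positive-versus-negative symptom model, but it is a consequence of infection and should not be adjusted for in that contrast

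*Protocol article*

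**What the plan says.** Section 2.7 of the protocol article describes the adjusted comparison as follows: "Multivariable models are used to test for the likelihood of (long-term) symptoms in positive vs. negative participants, adjusted for possible confounders". The sentence directly after it gives the candidates: "Possible confounders include age, sex, underling disease, severity of COVID-19, and year-quarter when tested". Only then does the text turn to a separate analysis: "Risk factor analyses, with post-COVID-19 condition as outcome, will be performed using multivariable logistic regression models".

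Table 2 (section 2.5) holds two kinds of item from which severity could be built. The row that begins "Treatment when tested (hospitalization, duration, and oxygen use" is asked of positives only. The row "Severity of symptoms" is asked of all participants. The article does not say which item defines severity of COVID-19, how negatives would be coded, or that the variable is confined to analyses among positives.

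Section 3.1 states the purpose of the negative group: including it "made it possible to identify symptoms and impact accountable to a SARS-CoV-2 infection".

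**The concern.** A confounder of positive versus negative must not be a result of being positive. Age, sex and year-quarter of testing meet that condition, and so does underlying disease if it was present before the test. Severity of COVID-19 does not: it arises because infection occurred, and it is one of the routes by which infection may lead to lasting symptoms. Holding it fixed removes that route from the estimate.

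Section 3.1 wants symptoms and impact attributable to infection, which is a total effect. An estimate adjusted for severity answers a different question, or none, depending on the coding. The article itself points the other way in section 3.1.1, where the possible confounders named are only sex, age and year-quarter of testing.

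**Working it through.** The article gives no sample size, power or effect figure for this model, so there is no stated result to reproduce. The check takes each way in which severity could be entered. The structure comes from section 2.7 and Table 2. **All risks and severity shares below are assumed**, because the documents give none.

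**1. Treatment items, negatives as their own 'none' level.** Take the columns intercept, positive, mild, severe. The three distinct rows are negatives (1,0,0,0), mild positives (1,1,1,0) and severe positives (1,1,0,1). Since positive = mild + severe, the four columns have rank 3 and the positive-versus-negative coefficient is not identified. If software drops a column silently, the meaning of the remaining coefficient depends on which one: without the mild column, positive means mild versus negative; without the severe column, it means severe versus negative. Sample size does not help. The article reports "Invited for participation were 41,780 PCR COVID-19 positives and 19,875 negatives from test records registered in the registry" (41,780 + 19,875 = 61,655), and the rank is 3 for any group sizes.

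**2. Treatment items, severity missing for negatives.** A complete-case fit drops everyone not asked the items, so the comparison group disappears. Routing follows the self-reported test result. If the exposure is the registry result, the only negatives retained would be those who reported themselves positive, which is not a usable control group.

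**3. Treatment items, negatives coded at the lowest level.** The model can be fitted. With one severe/not-severe indicator it is saturated over three cells, so

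- adjusted OR = odds(mild positives) / odds(negatives)
- total OR = odds(all positives) / odds(negatives), where the risk in all positives = (1 − s) × mild risk + s × severe risk, and s is the severe share.

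With assumed risks of 20% (negatives), 35% (mild) and 70% (severe), the adjusted OR is (0.35/0.65)/(0.20/0.80) = 2.15 for every s. For s = 2% the risk in all positives is 0.98 × 0.35 + 0.02 × 0.70 = 0.357, so the total OR is (0.357/0.643)/0.25 = 2.22. The other values follow in the same way:

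| Severe share | Total OR, risks 20/35/70% | Adjusted OR | Total OR, risks 20/25/60% | Adjusted OR |
|---|---|---|---|---|
| 2% | 2.22 | 2.15 | 1.38 | 1.33 |
| 5% | 2.32 | 2.15 | 1.46 | 1.33 |
| 10% | 2.50 | 2.15 | 1.59 | 1.33 |
| 20% | 2.90 | 2.15 | 1.88 | 1.33 |

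**4. Symptom severity, asked of everyone.** The model can be fitted, but in negatives the item is not severity of COVID-19, and in positives it is partly produced by the infection. Assume logit(risk) = −2 + 0.5 × positive + 1.5 × high severity. The adjusted OR is exp(0.5) = 1.65. The cell risks are:

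- positives: 50.0% (high severity), 18.2% (low)
- negatives: 37.8% (high), 11.9% (low).

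With high severity in 60% of positives and 30% of negatives:

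- positives: 0.6 × 0.500 + 0.4 × 0.182 = 0.373
- negatives: 0.3 × 0.378 + 0.7 × 0.119 = 0.197
- total OR = (0.373/0.627)/(0.197/0.803) = 2.43 (computed from unrounded risks).

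With 70% and 40% the total OR is 2.38. The gap to 1.65 is not an artefact of odds ratios being non-collapsible: without mediation or confounding, the unadjusted OR would be the one closer to 1.

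**The case against.** The strongest reply is about wording. The list is introduced as possible confounders, the section closes by calling its contents examples, and the risk-factor models, where severity is a natural covariate among positives, come in the very next sentence. The list may be a common pool from which each model draws, with the selection left to an analysis plan that is not shown. That softens the point but does not remove it. By position the list belongs to the positive-versus-negative model, severity is named and not merely left open, and nothing confines it to positives. If one pool was meant for both models, the text has to separate them, because severity fits only one.

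A second reply is that the model can be fitted, since Table 2 asks symptom severity of all. This is correct. A reader might infer that the infection effect cannot be estimated at all, but the documents do not support that: non-identification follows only if severity comes from the positives-only items and negatives form their own level or are missing. Coding negatives at the lowest level also gives an interpretable contrast, though not the total effect.

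A third reply is that section 2.7 first answers the prevalence question descriptively, with confidence intervals and with symptom prevalence in negatives alongside. That stands. None of it uses severity, so only the adjusted model is affected.

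One might add that the negatives "might include some COVID-19 positive cases", as section 2.6.2 acknowledges, so that some do have a COVID-19 severity. It would still be a consequence of infection, and Table 2 does not list the acute-treatment row for negatives.

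**Conclusion.** The point holds. Severity of COVID-19 is wrong as an adjustment variable in the positive-versus-negative model, because it follows from the exposure. What goes wrong depends on the coding: the contrast is not identified, or becomes mildest positives versus negatives, or conditions on a consequence of infection.

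The direction is understatement of the total effect, provided that severity raises the risk of lasting symptoms and, for the item asked of everyone, that infection also raises severity. The size cannot be derived from the documents. Under the assumed inputs it runs from small (2.15 against 2.22 with 2% severe) through moderate (2.15 against 2.90 with 20% severe) to substantial (1.65 against about 2.4 with graded symptom severity in everyone).

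A reader might also infer that most of the infection effect would vanish. Steep assumptions produce that: with positives 70/25/5% mild/moderate/severe, risks of 20/40/60%, and 15% in negatives, the excess falls from 27 − 15 = 12 points to 20 − 15 = 5. The documents give neither those shares nor those risks, and the introduction says that most infections are mild, so this is one scenario and not an estimate.

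**What to change.** In section 2.7, or in the analysis plan that implements it, give the two kinds of model separate covariate lists:

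- **Positive versus negative:** adjust for age, sex, year-quarter of testing and underlying disease present before the test. Remove severity of COVID-19. Table 2 already asks all participants about the origination of underlying disease, which should help restrict that variable to conditions that predate the test.
- **Positives only:** use severity in the risk-factor models, and state which Table 2 item or items define it.
- **Optional:** to show how the excess varies with severity, present positives by severity stratum, each against the negatives, labelled as a description and not as an adjusted infection effect.

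The cost is about one sentence, with no new data collection and no change to the descriptive prevalence analysis.

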Currently, the impact of health problems after a SARS-CoV-2 infection are not fully understood, also the prevalence and incidence of post-COVID-19 condition are still unclear. Reasons for this unclarity include difficulties encountered in studying post-COVID-19 condition. In previous scientific studies, this translated into the inclusion of participants without a formal diagnosis of an acute infection, due to the lack of PCR test capacity in the first wave (15), and long-term symptoms after an acute infection (13), due to the lack of a globally accepted case definition at that time before the release of the recent WHO definition. Furthermore, study participants were followed at different time points since infection, participants represented a selected population instead of a population-based population, being included from hospital-based settings (16), medical records (17), peer support groups (9), or social media platforms (18). Furthermore, in many studies, a control or reference group of negatives was lacking (19). Including specific study populations may lead to selection bias and alongside with the lack of harmonization of measures, these limitations hamper the comparison between studies, for instance regarding prevalence, incidence, and impact on health or socioeconomics (20). Furthermore, established risk factors for post-COVID-19 condition are, for example, female sex and pre-existing co-morbidities (21–23), but there are still knowledge gaps on risk factor coherence and possible protecting factors (for example vaccination) for post-COVID-19 condition.

The current study, called Prevalence, Risk factors and Impact Evaluation of post-COVID-19 condition (PRIME post-COVID) study, was set up to gain more insight into the occurrence and impact of post-COVID-19 condition in the community, by including a large-scale population-based PCR positive sample, a negative control group, and follow-up measures for prospective assessment. The findings of this study will contribute to the development of holistic social and health care pathways and support systems. Here, the design and recruitment are described.

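### The confounder set named for the positive-versus-negative symptom model is poorly chosen: it lists severity of COVID-19, a consequence of infection, and does not name pre-test vaccination or education

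*Protocol article*

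**What the plan says.** Section 2.7 of the protocol article describes the comparison: "Multivariable models are used to test for the likelihood of (long-term) symptoms in positive vs. negative participants, adjusted for possible confounders". The next sentence gives the adjustment variables: "Possible confounders include age, sex, underling disease, severity of COVID-19, and year-quarter when tested". The paragraph closes by describing its own status: "These are examples of analyses to answer a main study question".

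Table 2 (Section 2.5) shows what is available. Asked of all participants are "Level of education", "Vaccination status", the dates and types of vaccination, the test date, and "Smoking and substance". Treatment when tested, which covers hospitalization, its duration and oxygen use, is asked of positives only.

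Section 2.2 samples negatives within strata of age, sex, year-quarter of test and municipality. Vaccination, education and smoking are not strata.

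Vaccination does appear elsewhere in the article. The Introduction counts it among "possible protecting factors (for example vaccination) for post-COVID-19 condition", and the second study question in Section 2 gives it as an example of a risk factor. Neither place treats it as a confounder of positive versus negative.

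**The concern.** Section 3.1 credits the test-negative group with making it possible to identify symptoms that are due to the infection. That reading needs control of common causes of the test result and later symptoms, and no adjustment for consequences of infection. The named set falls short in two ways.

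First, severity of COVID-19 lies on the path from infection to later symptoms. Adjusting for it removes part of the effect that the contrast is meant to measure.

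Second, vaccination completed before the test precedes the exposure and may plausibly affect both the test result and later symptoms. Level of education may do the same through exposure, testing behaviour and background health. Sampling does not balance either of them. Adjusting for pre-test vaccination here is not over-adjustment, and it is a separate matter from studying vaccination as a risk factor among positives.

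**Working it through.** The article gives no effect size, and no distribution of vaccination, education or smoking by test result. There is therefore no stated figure to reproduce.

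**1. Severity.** Let *b* be the symptom risk in negatives, *s* the share of positives with severe disease, and *r1* and *r0* the risks in severe and non-severe positives.
- Total excess = (1 − s)·r0 + s·r1 − b.
- If negatives are coded non-severe and severity enters as a main effect, the coefficient for a positive test on the risk scale estimates r0 − b.
- Difference = s·(r1 − r0).

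The adjusted contrast is too small whenever severe cases have more lasting symptoms. If severity is instead left blank in negatives, they drop out of the model. Table 2 does ask severity of symptoms of everyone, but in a negative that is not severity of COVID-19.

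**2. What Table 1 says about timing.**
- Tested in 2021, positives: (9,341 + 9,561 + 6,106 + 3,947)/41,780 = 28,955/41,780 = 69.3%.
- Tested in 2021, negatives: (4,255 + 3,635 + 2,483 + 1,156)/19,875 = 11,529/19,875 = 58.0%.
- Tested in the 2nd or 3rd quarter of 2020: 765/41,780 = 1.8% of positives and 2,628/19,875 = 13.2% of negatives.

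Even a stratified variable differs between the invited groups, so balance on unstratified ones cannot be presumed. Year-quarter is in the named set and deals with calendar time. It does not deal with who was vaccinated within a quarter.

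**3. Possible size if the named set were used alone.** For one binary confounder with prevalence p1 in positives and p0 in negatives, and risk ratio RR for symptoms, the bias factor is [1 + p1(RR − 1)]/[1 + p0(RR − 1)]. All inputs below are assumptions. Points are for an assumed 25% background.
- Vaccination, RR 0.7, 20% v 30%: 0.94/0.91 = 1.033 (0.8 points).
- Vaccination, RR 0.5, 30% v 50%: 0.85/0.75 = 1.133 (3.3 points).
- Low education, RR 1.2, 35% v 30%: 1.07/1.06 = 1.009 (0.2 points).
- Low education, RR 1.5, 40% v 30%: 1.20/1.15 = 1.043 (1.1 points).
- Smoking, RR 1.2, 12% v 18%: 1.024/1.036 = 0.988 (−0.3 points).
- Smoking, RR 1.5, 10% v 20%: 1.05/1.10 = 0.955 (−1.1 points).
- Any of the three with equal prevalence, or with RR 1: exactly 1.000.

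**4. Plausibility of the vaccination inputs.** Assume nobody was vaccinated before a 2020 test. Then 50% of negatives means 0.50/0.580 = 86% of those tested in 2021, and 30% of positives means 0.30/0.693 = 43%. The factor 1.133 is therefore a demanding extreme. If instead the same share *v* of 2021 tests followed vaccination in both groups, crude prevalence is 0.693v in positives and 0.580v in negatives. For a protective vaccine the crude factor then falls below 1. That part would be absorbed by year-quarter, and what remains is the within-quarter difference, on which the article gives nothing.

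**The case against.** The strongest reply is that the list is not closed. It is introduced as possible confounders, the paragraph calls its content examples, and Section 3.1 says that the broad questionnaire allows correction for several confounders. A full covariate list commonly sits in an analysis plan, which is not shown. This stands. A reader might infer that the study's estimate will retain avoidable confounding, but the article never says that the five variables are the whole set or that the others will be left out.

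The magnitudes are also open to challenge. Every input is assumed. The factors are crude and take no account of age, sex, underlying disease and year-quarter, which are already named and may absorb part of any imbalance. The directions conflict, with vaccination and education above 1 and smoking below 1 in the scenarios used. A reader might take the largest value over a small assumed excess as the expected bias, and the article supports no such figure.

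Third, a reader might want smoking in the main set because dyspnoea is one of the outcome definitions. Table 2 gives the item no time reference. The questionnaire could follow the test by up to about 19 months (1 June 2020 to 9 January 2022), and illness may have changed smoking habits. Requiring it would risk the same post-exposure adjustment as severity.

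These replies do not rescue the variables that the article chose to name. Severity is listed explicitly, and vaccination is left out of this list although the article twice marks it as relevant to the condition.

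**Conclusion.** The point holds as a criticism of the stated set. Naming severity of COVID-19 as a confounder of positive versus negative is wrong in principle. If it is used, it shifts the risk-difference contrast by s·(r1 − r0), an amount that the article does not allow to be evaluated. Not naming pre-test vaccination and education is a weaker fault: both are collected from everyone, neither is a stratum, and vaccination has the clearer claim of the two.

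Residual confounding from these omissions is conditional on the named set being used unchanged. Under the assumed inputs it runs from none to about 13% on the risk ratio for vaccination and to about 4% for education. Neither size nor sign can be derived from the document, and no established bias should be claimed. The correction is worth making because the attribution of symptoms to infection rests on this contrast and the data are already in hand.

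**What to change.** In Section 2.7, state the adjustment set for the positive-versus-negative model as age, sex, test quarter, underlying disease present before the test, vaccination status at the test date (counting only doses dated before the test) and level of education. Remove severity of COVID-19 from this model; it may stay in analyses confined to positives. Report the estimate with and without vaccination and education, so that readers see what they change. Add smoking in a sensitivity analysis only, with a note that it is reported at the questionnaire.

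The cost is a change of wording and a few extra model terms, with no new data collection. The downside is reliance on self-reported vaccination dates, and restricting underlying disease to pre-test conditions depends on what the Table 2 item on its origination records.
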